# Real versus sham proximal biofield therapy in the treatment of warts of the hands and feet in adults: study protocol for a randomized controlled trial (MAGNETIK study)

**DOI:** 10.1186/s13063-017-1994-4

**Published:** 2017-06-07

**Keywords:** Biofield therapy, Alternative medicine, Warts, Papillomavirus infections, Randomized controlled trial, Single-blind and assessor-blind method

## Abstract

**Background:**

Despite the lack of scientific studies on biofield therapies, they are widely acclaimed by patients. The mechanisms of action are not explained by current allopathic medical approaches. Warts are common and contagious viral lesions that may be refractory to standard dermatologic treatments such as cryotherapy, laser therapy, and keratolytic ointments. Biofield therapies are efficient in various pathologies. Their ability to treat warts has never been demonstrated in a scientific study with a robust methodology. Patients with refractory warts often place their trust in these alternative therapies because of the poor results obtained from traditional medicine. We propose a prospective, randomized, single-blind, assessor-blind trial to evaluate the efficacy of treatment of warts by biofield therapy.

**Methods/design:**

Subjects with warts on their feet or hands will be randomized into two groups: real biofield therapy versus sham therapy. The diagnosis will be made at the time of inclusion, and follow-up will take place in week 3. Comparison of pictures of the warts at baseline and after 3 weeks will be used as the primary outcome measure. The hypothesis is that the extent of the disappearance of the original wart in the group treated by real biofield therapy will be 70% and that it will be 30% in the group treated by sham therapy. Using 90% power and an alpha risk of 5%, 31 subjects are required in each group for a two-tailed proportion comparison test.

**Discussion:**

To our knowledge, this is the first study to evaluate the efficacy of biofield therapy on warts. Therefore, the aim of this study is to extend knowledge of biofield therapy to another area of medicine such as dermatology and to propose complementary or alternative practices to improve patient well-being. The main strength of the study is that it is a randomized, single-blind, assessor-blind, placebo-controlled study.

**Trial registration:**

ClinicalTrials.gov identifier: NCT02773719. Registered on 22 April 2016.

**Electronic supplementary material:**

The online version of this article (doi:10.1186/s13063-017-1994-4) contains supplementary material, which is available to authorized users.

## Background

The concept of biofield therapies originates from many different cultures over thousands of years [1]. Currently, biofield therapies are used increasingly in modern-day healthcare and have only recently been studied by conventional scientific methods to evaluate their actual effects. Biofield therapies are defined as noninvasive, practitioner-mediated practices that stimulate the healing response in patients. Biofield therapies show strong evidence of reducing pain intensity in pain populations and moderate evidence of reducing pain intensity in hospitalized and cancer patient populations [2]. Authors of a recent review [3] reported 18 clinical trials on biofield therapies with a high level of evidence, among which 12 had at least one primary outcome with statistically significant beneficial treatment. More moderate evidence in a nonrandomized study showed a decrease in depressed mood [4] or reduced pain after biofield therapies in populations with cancer [5]. These healing practices involve electromagnetic fields that are delivered either proximally (with the practitioner and the receiver in the same room) or distally. Biofield therapy produces a wide variety of clinically significant effects, including growth enhancement, wound repair, regeneration, and reduction of pain [6–10], but, to our knowledge, nothing has been studied to date in the treatment of warts. Palmar or plantar warts are one of the most common infectious skin diseases caused by the human papillomavirus. Even if warts are benign skin growths that disappear over time without treatment, they remain unsightly and contagious and can cause significant discomfort. The main topical treatments for cutaneous warts are summarized in a Cochrane review [11]. Salicylic acid and cryotherapy stand out as the most commonly used treatments, but they remain only moderately effective. Resistance of warts to conventional therapies leads some patients to use alternative medicine such as biofield therapies, and most of them report positive results. At this stage, however, there is no clear or convincing scientific evidence to prove a positive effect. Despite controversies and current gaps in research studies, biofield therapies are widely used by a significant number of patients. Some believe that this response derives partly from the placebo effect.

The purpose of this study is to objectively determine the impact of biofield therapies on wart treatment after a single session according to the main recommendations of clinical studies on biofield therapies [12]. To this end, we designed a study protocol with the appropriate methodology in which patients are treated either by a certified biofield therapist or a sham therapist who mimics all procedures used by the biofield therapist (i.e., placebo group).

## Methods/design

### Study design

This protocol was developed in accordance with the Standard Protocol Items: Recommendations for Interventional Trials (SPIRIT) Statement. For the SPIRIT checklist see Additional file 1. The MAGNETIK study is a prospective, randomized, placebo-controlled, single-blind, assessor-blind trial. The purpose of this study is to evaluate the benefit of biofield therapies on common feet or hand warts when practiced by a real or placebo practitioner.

### Study population

A total of 62 subjects will be included in this trial. Thirty-one patients will receive biofield therapy delivered by a certified practitioner, and 31 patients will be assigned to the placebo arm with a sham therapist. The participant timeline is shown in Fig. 1.

**Fig. 1 Fig1:**
[figure not shown]
Schedule of enrollment, interventions, and assessments

### Eligibility

Patients with common warts on the hands or feet for at least 3 months are eligible for the study. Patients meeting one or more of the following criteria will not be included:Lack of informed consent prior to randomizationLess than 18 years old or under legal protectionTreated with oral corticotherapy for more than 6 monthsImmunosuppressed or with a history of transplant surgeryUndergoing chemotherapy or suspected to have cancerous wartsPatients with infected warts; injured warts; already treated for 90 days with chemical processes, medical devices, or surgery; or already having received biofield therapy

Subjects will be excluded from the study if their warts are treated with other treatment during the protocol. The appropriate examinations will be performed to ensure that subjects meet all the criteria. The subjects are free to leave the study at any time. Occurrence of adverse events can also lead to discontinuation.

### Recruitment

Subjects will be recruited by an advertising and information campaign at dermatologists’ practices and general practitioners’ practices in or near Caen, France.

### Random allocation

Randomization will be performed using an interactive web response system with Ennov Clinical® Software (Ennov, Paris, France). Trial participants and dermatologists assessing outcomes are blinded to allocation; however, the study nurses and sponsor are not.

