### Study protocol

All study procedures take place at the clinical research unit in Caen University Hospital, Caen France. First (i.e., at enrollment), after written informed consent is obtained, the dermatologist establishes a diagnosis of warts on the feet and/or hands and then performs mapping to record warts one by one. Each wart is individually numbered to correlate measurements (baseline vs. W3) or original wart designation (*see below*) to the initial mapping. Before the intervention (W0), each wart is photographed (baseline picture) by the study nurse in accordance with location and number label drawn on the map. The subject is interviewed about beliefs (i.e., by questionnaire) about biofield therapies and is treated according to randomization by either the real or the sham practitioner. The intervention consists of a single session of biofield therapy performed by a real or sham therapist and usually takes about 40 minutes.

The French organization for alternative medicines (the Groupement national pour l’organisation des médecines alternatives [GNOMA]) was asked to validate the skills of the study practitioners. For this purpose, two independent experts from the GNOMA attended a training session. They concluded on the biofield therapeutic abilities of the real practitioner and confirmed the sham therapist, also known as the placebo, to have no biofield therapeutic abilities. The placebo therapist learned the movements during training sessions in order to reproduce the gestures used by the real practitioner.

When the therapist meets the subject (W0), he or she assesses the subject’s level of energy and asks the subject what the subject perceives while (1) facing the subject, with hands placed at either side of the subject’s face (the therapist expects the subject to feel heat or dizziness); (2) with hands placed above the shoulders in an attempt to rock the subject forward and backward; and (3) with hands placed on the middle of the subject’s back (heat should be felt), then on the lower back (cold should be felt). If the subject’s perception is too poor, meaning the subject’s energy level is too low, the therapist then magnetizes the plexus area in a horizontal line before treating the warts. When the subject’s energy level has been assessed, the wart is treated.

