The therapist first magnetizes using the index finger placed on top of each wart. Where there are multiple warts, the therapist identifies the original wart and, with the other hand, follows the path of the wart, hooks a finger above it while saying that the wart has been caught, and asks if the subject can feel it. The therapist then pulls on the wart with the finger, as if pulling a thread, until the subject says he or she no longer feels anything. At the end of the session, the therapist checks that the subject no longer feels anything and provides the subject with some recommendations concerning the wart, such as avoiding contact with water or avoiding physical exercise within the next 24 h. The therapist explains that, after few days, a black thread will appear on the wart. If this occurs, the patient is asked to cover it with a plaster.

The subject then returns home and comes back to the clinical research unit for a follow-up visit 3 weeks later. The 3-week visit is scheduled to assess whether the warts have disappeared. Another picture is taken by a study nurse in the same conditions as those at baseline. The subject is interviewed about any treatments taken during this period. Patients are excluded if they use any wart treatment. Six weeks postintervention (W6), the subject will be contacted by a study nurse to assess wart disappearance and to ensure that no medical wart treatments were used. All interventions and assessment time points are presented in Fig. 1.

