### Primary outcome measurement

The primary outcome is the disappearance of the original wart between W0 and W3. The dermatologist qualifies each wart—the original wart and the others—without knowing which one is designated by the therapist as being the original one. The study nurse then decodes which is the original wart and collects the data in the electronic case report form. At the end of the study, pictures of warts at W0 and W3 are evaluated by a blinded dermatologist using Mesurim® software to measure the mean diameter of each wart numbered and mapped. Data are recorded in a separate file with a picture code only. The percentage reduction in each wart will be calculated using the mean diameter of each wart at W0 and W3 by the data analyst.

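### The six-week wart disappearance outcome is collected by a nurse who knows the allocation, so the unqualified assessor-blind label does not cover it

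*Protocol article*

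**What the plan says.** The Study design section describes the trial as follows: "The MAGNETIK study is a prospective, randomized, placebo-controlled, single-blind, assessor-blind trial". The Discussion part of the abstract presents this as its chief merit: "The main strength of the study is that it is a randomized, single-blind, assessor-blind, placebo-controlled study". The main Discussion repeats the claim. None of these places limits it to particular outcomes or visits.

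The Random allocation section says who is blinded: "Trial participants and dermatologists assessing outcomes are blinded to allocation; however, the study nurses and sponsor are not".

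Study nurses then have three tasks that touch outcome data:

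- **W6 call.** Under Study protocol, "the subject will be contacted by a study nurse to assess wart disappearance and to ensure that no medical wart treatments were used". Secondary outcome measurements confirms that W6 disappearance is obtained by telephone.
- **W3 photograph.** Under Study protocol, "Another picture is taken by a study nurse in the same conditions as those at baseline". The baseline picture is also the nurse's task, but it precedes treatment: "each wart is photographed (baseline picture) by the study nurse in accordance with location and number label drawn on the map".
- **Decoding.** Under Primary outcome measurement, once the dermatologist has rated every wart: "The study nurse then decodes which is the original wart and collects the data in the electronic case report form".

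The same section says that the rating dermatologist does not know which wart the therapist designated. It also says that the W0 and W3 pictures are measured by a blinded dermatologist and that the measurements are filed under a picture code alone.

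**The concern.** Random allocation names only the dermatologists as blinded assessors, and no dermatologist takes part at W6. There the nurse asks the question, interprets the answer and records whether the wart has gone, knowing which practitioner treated the participant. Follow-up questions, the handling of an uncertain answer, or a cue given during the call could differ between arms. The same call checks for other wart treatments, so that information is also gathered with the arm known.

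At stake is the credibility of the W6 comparison and the accuracy of the blinding claim in the report. A reader who takes the label at face value would assume that W6 has the same protection as W3.

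There is a smaller matter at W3. Someone who knows the arm takes the follow-up picture, and later links the dermatologist's ratings to the designated wart. A blinded reader cannot undo a difference introduced when the image is taken. In participants with several warts, the link decides which rating becomes the primary datum.

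**Working it through.** **Step 1. Who does what, and with what knowledge** (all from the Methods of the protocol article)

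| Step | Done by | Knows the arm? | Nature of the step |
|---|---|---|---|
| W0 photograph | study nurse | taken before the intervention | image capture |
| W3 rating of each wart | dermatologist | no, nor which wart is the original | outcome assessment |
| W3 photograph | study nurse | yes | image capture |
| Decoding and eCRF entry | study nurse, after the rating | yes | data handling |
| Measurement of W0 and W3 pictures | dermatologist, coded pictures | no | outcome assessment |
| W6 disappearance | study nurse by telephone, from the participant's report | nurse yes, participant no | outcome elicitation and recording |

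Both W3 assessment steps are blinded. The only step where an outcome is obtained with no blinded assessor is W6.

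**Step 2. The plan's own sample size**

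Inputs from Sample size calculation: 70% v 30%, two-sided alpha 5%, power 90%, arcsine method.

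- h = 2·asin(√0.70) − 2·asin(√0.30) = 0.823
- n per arm = 2·((1.960 + 1.282)/0.823)² = 31.02

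The stated 31 per arm is reproduced, rounding to the nearest whole number. The blinding point does not affect it.

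**Step 3. Illustration for W6 only**

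Assumptions:

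- The true W6 disappearance rate is 30% in both arms. This borrows the plan's sham rate for W3; the article gives no W6 rate.
- There are 31 participants per arm, all with a W6 answer.
- A fraction f of persistent warts in the real arm is recorded as gone, and none in the sham arm. The article gives no basis for any value of f.

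Recorded rate in the real arm = 0.30 + 0.70·f

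- f = 10%: 0.30 + 0.70 × 0.10 = 0.37
- f = 20%: 0.30 + 0.70 × 0.20 = 0.44

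With 31 × 0.70 = 21.7 participants expected to have a persistent wart, these are about 2.2 and 4.3 misrecorded answers.

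The chance of p < 0.05 is the sum of the binomial probabilities over all pairs of counts (0 to 31 in each arm) for which the test rejects. Both tests are listed under Statistical methods; Pearson is used without continuity correction.

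| f | Recorded rates | Fisher | Pearson |
|---|---|---|---|
| 0 | 30% v 30% | 2.7% | 5.0% |
| 10% | 37% v 30% | 5.4% | 8.9% |
| 20% | 44% v 30% | 14.2% | 20.8% |

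At f = 10% the false-positive rate rises modestly. At f = 20% it is roughly four to five times its unbiased value.

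**The case against.** The strongest reply is that the article is open about who is unblinded and names the dermatologists as the blinded assessors, so the label is true where it matters most. The W6 informant is a blinded participant, W6 is secondary, and a call script is the kind of detail that an article leaves to the full protocol. The bias fractions are also assumed. Most of this stands. The article cannot be faulted for omitting a script, and no figure in it supports a particular amount of misrecording. The reply does not reach the label itself: the article gives the assessing of disappearance at W6 to the nurse, "the subject will be contacted by a study nurse to assess wart disappearance", and nowhere restricts the assessor-blind claim to W3.

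A reader might go further and infer that the primary outcome has lost its blinding because nurses take the W3 picture and decode the original wart. The documents do not support that:

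- The W3 picture is to be taken under the baseline conditions and is measured under a code by a blinded dermatologist.
- The rating is made before the decoding, by someone who knows neither the arm nor the designated wart.
- The therapist identifies the original wart during the W0 session, and the wart numbering ties that designation to the initial map. Decoding is thus a look-up rather than a judgement, and with a single wart there is nothing to select.
- The article does not say when the designation enters the eCRF or whether it is locked. The full protocol may cover this, so its absence is not evidence of an unprotected step.

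What remains at W3 is a handling risk that is easy to close.

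**Conclusion.** The point holds for W6. That secondary outcome is elicited and recorded by staff who know the allocation, so the unqualified assessor-blind description is too broad. The blinded participant's report reduces the exposure without removing it. W3 photography and decoding are residual handling risks, and blinded assessment of the primary outcome is intact.

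The direction and size of any W6 bias are unknown. The rejection rates of 5% to 14% (Fisher) and 9% to 21% (Pearson) rest on an assumed one-sided misrecording of 10% to 20% and an assumed 30% true rate. They show what could happen, not what should be expected, and must not be carried over to the primary outcome. The change is worth making because it is cheap. The primary analysis does not depend on it.

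**What to change.** 1. Have the W6 call made by an existing research-unit member without access to the allocation, using a fixed script with set answer categories. Where the rota allows, have the same kind of person take the W3 pictures.
2. Record the therapist-designated wart number in the eCRF at W0, lock it, and merge it with the dermatologist's ratings by program, in place of manual decoding.
3. If the W6 call stays with the unblinded nurse, report W6 as not blind-collected and limit the assessor-blind statement to the W3 outcomes.

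The cost is some rota planning, access rights in the web system, a short script and one eCRF field. No new staff are needed, and the sample size and primary analysis do not change.

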### Study protocol

All study procedures take place at the clinical research unit in Caen University Hospital, Caen France. First (i.e., at enrollment), after written informed consent is obtained, the dermatologist establishes a diagnosis of warts on the feet and/or hands and then performs mapping to record warts one by one. Each wart is individually numbered to correlate measurements (baseline vs. W3) or original wart designation (*see below*) to the initial mapping. Before the intervention (W0), each wart is photographed (baseline picture) by the study nurse in accordance with location and number label drawn on the map. The subject is interviewed about beliefs (i.e., by questionnaire) about biofield therapies and is treated according to randomization by either the real or the sham practitioner. The intervention consists of a single session of biofield therapy performed by a real or sham therapist and usually takes about 40 minutes.

The French organization for alternative medicines (the Groupement national pour l’organisation des médecines alternatives [GNOMA]) was asked to validate the skills of the study practitioners. For this purpose, two independent experts from the GNOMA attended a training session. They concluded on the biofield therapeutic abilities of the real practitioner and confirmed the sham therapist, also known as the placebo, to have no biofield therapeutic abilities. The placebo therapist learned the movements during training sessions in order to reproduce the gestures used by the real practitioner.

When the therapist meets the subject (W0), he or she assesses the subject’s level of energy and asks the subject what the subject perceives while (1) facing the subject, with hands placed at either side of the subject’s face (the therapist expects the subject to feel heat or dizziness); (2) with hands placed above the shoulders in an attempt to rock the subject forward and backward; and (3) with hands placed on the middle of the subject’s back (heat should be felt), then on the lower back (cold should be felt). If the subject’s perception is too poor, meaning the subject’s energy level is too low, the therapist then magnetizes the plexus area in a horizontal line before treating the warts. When the subject’s energy level has been assessed, the wart is treated.

The therapist first magnetizes using the index finger placed on top of each wart. Where there are multiple warts, the therapist identifies the original wart and, with the other hand, follows the path of the wart, hooks a finger above it while saying that the wart has been caught, and asks if the subject can feel it. The therapist then pulls on the wart with the finger, as if pulling a thread, until the subject says he or she no longer feels anything. At the end of the session, the therapist checks that the subject no longer feels anything and provides the subject with some recommendations concerning the wart, such as avoiding contact with water or avoiding physical exercise within the next 24 h. The therapist explains that, after few days, a black thread will appear on the wart. If this occurs, the patient is asked to cover it with a plaster.

The subject then returns home and comes back to the clinical research unit for a follow-up visit 3 weeks later. The 3-week visit is scheduled to assess whether the warts have disappeared. Another picture is taken by a study nurse in the same conditions as those at baseline. The subject is interviewed about any treatments taken during this period. Patients are excluded if they use any wart treatment. Six weeks postintervention (W6), the subject will be contacted by a study nurse to assess wart disappearance and to ensure that no medical wart treatments were used. All interventions and assessment time points are presented in Fig. 1.

